### Outcomes

The primary outcome is paternal MH (stress) assessed by semistructured interviews.

The secondary outcomes are (1) maternal stress, assessed by the Parental Stressor Scale: Neonatal Intensive Care Unit (PSS:NICU) questionnaire; (2) paternal stress, assessed by the PSS:NICU questionnaire; (3) parental anxiety, assessed by the Generalized Anxiety Disorder Assessment-7 (GAD-7); (4) parental depression, assessed by the Personal Health Questionnaire-9 (PHQ-9); and (5); paternal engagement with FICare, assessed via interviews.

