### Phase 1 Study: Baseline Data Collection (9 Months)

#### Overview

Phase 1 will be conducted as follows: (1) Prior to the introduction of the study to wider NU clinical staff members, staff knowledge, experiences, and opinions about the role of fathers and FICare will be assessed by a questionnaire. (2) Once a parent is recruited, the PSS:NICU [26] and MH questionnaires (GAD-7 [27] and PHQ-9 [28]) will be given to complete within 7 days. (3) Fathers or partners will be invited to participate in 2 semistructured interviews, within 2 weeks of recruitment and immediately prior to discharge. The interviews will explore their MH, experiences of bonding with baby, understanding the neonatal environment, and reflecting on their service expectations. Based on the father’s or partner’s preference, interviews will be undertaken either in a private room on the NU or digitally via MS Teams at a mutually convenient time. Interviews will be digitally recorded and are anticipated to last up to 1 hour. Data saturation is expected at around 12-15 fathers. (4) The parents will be asked to complete the PSS:NICU, GAD-7, and PHQ-9 questionnaires at 3 weekly intervals, finishing on the week of discharge, to monitor their MH through their NU stay. (5) Up to 4 groups of 5 mothers will be invited to participate in a focus group to assess their wellbeing, experience of the NU, and their perspective on support for and from their partners. This will occur in a room in the NU at a time convenient to the mothers. Groups will be organized until data saturation is reached. (6) Telephone interviews and emailed questionnaires will be completed by parents at 4-6 weeks postdischarge to assess family confidence and bonding after NU discharge.

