### Phase 2 Study: Enhanced Father Involvement in FICare (9 Months)

Once a family is recruited, the program developed to enhance the father’s involvement in FICare will be implemented to take place at the parents’ pace (Table 2). Materials will be freely available to the study participants in a format suited to their needs (electronic or paper copy). All interested parents are encouraged to attend the peer support sessions, ward round participation, and bite-size education classes.

The NU experience and MH status of both parents will be assessed as in the phase 1 study (Figure 1) including assessing their experience of the FICare program. At the end of the phase 2 study, staff knowledge, experiences, and opinions about fathers and FICare will be reassessed and compared with the start of the study.

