### Questionnaires

For descriptive statistics, the median and mode scores of the PSS:NICU, GAD-7, and PHQ-9 will be used to describe the outcome of the questionnaires. For inference analysis, the difference in median for the PSS:NICU, GAD-7, and PHQ-9 at admission, discharge, and 6 weeks postdischarge will be compared between phase 1 and phase 2 using the Mann-Whitney test and the paired 2-tailed *t* test. The data will be checked for outliers and these will be corrected or removed. However, where these outliers are accurate, a nonparametric statistical analysis will be performed. Depending on the data type, missing data will be replaced with mean, median, or mode. In addition, regression and multiple imputations analysis will also be used to impute or generate missing values.

Staff survey questionnaire responses to individual questions will be presented as a percentage of individuals responding yes or no. The percentage of “yes” responses to each question by the staff at the start and end of the study will be compared by paired *t* test.

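### Questionnaire scores at admission are tested as an outcome rather than used as a baseline, later scores are compared unadjusted, and in phase 2 the admission form may follow the start of the programme

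*Protocol article*

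**What the plan says.** All references are to the protocol article.

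- **Between-phase analysis (Questionnaires).** The PSS:NICU, the GAD-7 and the "PHQ-9 at admission, discharge, and 6 weeks postdischarge will be compared between phase 1 and phase 2". The methods for this comparison are named as "using the Mann-Whitney test and the paired 2-tailed" t test. Regression appears only for missing data: "regression and multiple imputations analysis will also be used to impute or generate missing values".
- **Descriptive analysis (Questionnaires).** "For descriptive statistics, the median and mode scores of the PSS:NICU, GAD-7, and PHQ-9 will be used"; no time points are attached to this sentence.
- **Collection (Phase 1, Overview).** After recruitment the three questionnaires "will be given to complete within 7 days". Parents then complete the "questionnaires at 3 weekly intervals, finishing on the week of discharge", to follow their mental health during the stay, and again after discharge.
- **Phase 2.** The programme has the same trigger as the forms: "Once a family is recruited, the program developed to enhance the" father's part in FICare is put in place, at the parents' own pace. Assessments follow the phase 1 schedule.
- **Design.** The phases run one after the other at a tertiary and a level 2 unit, with gestation 22+0 to 32+6 weeks and up to 20 families per phase. Saturation is expected at about 12 to 15 fathers.

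**The concern.** The two phases contain different families, recruited at different times and not randomised. A gap in initial distress, in unit mix or in gestation can therefore arise by chance or by drift, and it passes into an unadjusted comparison of later scores. The study collects the one measurement best placed to deal with initial distress, the admission score, but the stated analysis uses it only as a further outcome. A between-phase test at admission says little about the programme, and without adjustment it does nothing to correct the later comparisons. Precision that needs no extra data is also given up.

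The 3-weekly scores enter no between-phase comparison, although the hypothesis in the Discussion covers symptoms during the hospital stay.

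Adjustment needs a baseline taken before exposure. If phase 2 parents can complete the first form after meeting the programme, that score may already carry some of its effect. Adjusting for it would then understate the benefit.

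**Working it through.** **The plan's own figure.** 20 families × 2 parents × 2 phases = 80 participants, as stated under Sample Size. It rests on qualitative saturation. The document gives no alpha, power, effect size, SD or correlation for the questionnaires, so those below are assumptions: two-sided alpha 0.05, and admission-to-follow-up correlation r = 0.3, 0.5 or 0.7.

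**How many tests fall at admission.** 3 scales × 3 time points × 2 parents = 18 between-phase tests per method, of which 3 × 2 = 6 are at admission.

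**Precision gained by using the admission score.** The variance factor is 1 − r², and the equivalent unadjusted number is 20/(1 − r²). The difference detectable with 80% power, in SD units, is (1.96 + 0.84) × √(2/n) × √(1 − r²).

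| | Unadjusted | r = 0.3 | r = 0.5 | r = 0.7 |
|---|---|---|---|---|
| Variance factor | 1 | 0.91 | 0.75 | 0.51 |
| Equivalent n for 20 per phase | 20 | 22 | 27 | 39 |
| Detectable difference, 20 per phase | 0.89 | 0.85 | 0.77 | 0.63 |
| Detectable difference, 15 per phase | 1.02 | 0.98 | 0.89 | 0.73 |

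A simulation (10,000 runs, normal data, 20 per phase, adjustment for admission score only) agrees. For a true effect of 0.5 SD, power is about 32% with Mann-Whitney and 36%, 42% or 56% with ANCOVA at the three correlations. For 0.8 SD it is about 67% against 72%, 80% or 93%.

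**Chance imbalance at admission.** If the phases do not truly differ, the difference in mean admission score has SD √(2/n). A gap above 0.3 SD then has probability 2 × P(Z > 0.3/√(2/n)), which is 34% at n = 20 and 41% at n = 15. A 0.3 SD gap carries 0.3 × r = 0.09, 0.15 or 0.21 SD into an unadjusted follow-up comparison.

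**Effect of a late phase 2 form.** If a share f of the programme effect is already present in the admission score, ANCOVA recovers 1 − r × f of the true effect. With f = 0.5 (assumed) this is 85%, 75% or 65%.

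**Cost in degrees of freedom.** Three covariates use 3 of 2n − 2, which is 22 at n = 12 and 38 at n = 20.

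**The case against.** The strongest reply is about stakes. The primary outcome is paternal stress assessed by interview. The Discussion says that the questionnaires support the qualitative data and test the feasibility of longitudinal collection, and that a larger sample would be needed to base the study on them. This stands, and it limits the weight of the point. It does not remove it, because the Questionnaires section commits to inferential tests.

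Other replies also stand in part:

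- **The gain depends on r.** Stays can last months, so r may be low. At 0.3 the gain is only about 10% (20 parents act like 22).
- **Contamination is possible, not certain.** Recruitment triggers both the forms and the programme, and the article does not order them. The GAD-7 and PHQ-9 look back a fortnight, so a form completed on day 7 covers at most 7/14 = half programme time. The article gives no such look-back period for the PSS:NICU.
- **Form order is not a complete cure.** All clinical staff are trained before phase 2, and Table 2 opens several sessions to any parent in the unit.
- **Period effects remain.** No covariate here separates the programme from calendar time.

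Some stronger readings are tempting but unsupported:

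- A reader might infer that fathers and mothers are pooled, because the Outcomes list has "parental anxiety, assessed by the Generalized Anxiety Disorder Assessment-7 (GAD-7") and likewise parental depression. That wording says whose anxiety is measured. No pooled test is stated and the Objective separates the parents, so no inflated error rate from correlated couples can be charged to the plan.
- A reader might infer that the 3-weekly scores go unanalysed. The descriptive sentence names no time points and may cover them. They are absent only from the between-phase tests.
- A reader might use the 900 and 600 annual admissions to size the imbalance between units. Those are all admissions, not infants under 33 weeks.
- The paired t test cannot be read as a within-person change analysis, since the sentence compares phases and these hold different families.

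**Conclusion.** The point holds as a concrete, low-cost improvement to a stated secondary analysis. The plan fixes admission as a tested outcome and compares later scores without adjustment, in small consecutive cohorts from two different units. Adjusting for admission score makes 20 parents per phase worth about 22, 27 or 39, at assumed correlations of 0.3, 0.5 and 0.7: a minor gain at the low end and a substantial one from 0.5 up. It also reduces confounding by initial severity and, with site and gestation added, by measured case mix. Period effects and unmeasured differences are left untouched.

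The timing point holds as a risk. Under the stated schedule the phase 2 baseline can be partly post-exposure, and adjusting for such a score would understate the effect. Form order should therefore be settled together with the adjustment. The qualitative primary outcome is not affected.

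**What to change.** 1. For families still to be enrolled in phase 2, have the admission questionnaires completed before programme materials or classes are given. Record the date of completion and the date of first programme contact, so that late forms can be identified.
2. For fathers and mothers separately, compare discharge and 6-week scores between phases by ANCOVA, or a rank-based equivalent, on admission score with site and gestation as covariates. Report the adjusted difference with its 95% confidence interval.
3. Show admission scores by phase descriptively only, without a test.
4. Optionally, use the 3-weekly scores in a mixed model. With perhaps 12 to 20 fathers per phase and a number of scores that varies with length of stay, this should not be the main analysis.
5. State in the report that period effects remain, and that staff training and open sessions may leave some early exposure.

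The cost is a few lines of analysis text, one instruction on form order with two dates to record, and about 3 degrees of freedom of roughly 22 to 38. No questionnaire is added. Form order cannot be changed for families already enrolled; 22 families across the study had been recruited by October 2023.

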## Abstract

**Background:**

Neonatal unit (NU) admissions for premature babies can last for months, which can significantly impact parental mental health (MH) with symptoms of depression, stress, and anxiety. Literature suggests fathers experience comparable MH symptoms to mothers. Family integrated care (FICare) is a culture where parents are collaborators and partners in caring for their hospitalized newborns. FICare improves infant outcomes and maternal MH. Similar reports on fathers are limited.

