#### Inclusion Criteria

The inclusion criteria are as follows: (1) parents of 22^+0^ to 32^+6^ weeks preterm infants; (2) infants aged 1 to 7 days; (3) infants with 2 primary caregivers (the father’s or partner’s participation in the study is a must, and participation from both parents is ideal), and (4) the parents should have conversational English.

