### Washout Period, Phase 2 Preparation (4 Months)

A program to enhance father participation with the FICare model will be developed using the existing Neonatal DadPad or Imperial Family Delivered Neonatal Care app. Both of these apps are currently used in several NHS Trusts to guide fathers through their NU journey. The phase 1 and systematic review findings, along with guidance from the PAG will inform our decision for what is best suited for our local population.

Teaching sessions will be undertaken to educate and upskill all clinical NU staff on the study aims, recruitment, phase 1 study findings, and upcoming phase 2 study, highlighting the importance of fathers’ role in the FICare (eg, teaching parents how to safely give nasogastric feeds and nappy changes in a ventilated baby). In addition, there will be regular FICare teaching for staff, including encouragement of parents to attend ward rounds, and with guidance to parents in the workbook (Table 2).

**Table 2 table2:** Program to enhance father involvement in family integrated care.

Strategies	When	Who
Educational booklet or app, including Introduction to the neonatal unit Meeting the multidisciplinary team—tailored to the individual unit Family integrated care Taking care of yourselves Routine care and “observations” Breastfeeding Developmental care Medications Nutrition and growth Ventilation and breathing support Cardiac (heart) conditions Gastrointestinal and liver (gut) conditions Brain development Planning for discharge Eyes	At parents’ disposal	Both parents
Suggested tasks or workbook, including Kangaroo care Nappy changes in incubator Mouth care and cleaning of baby Reading of observations (heart rate, temperature, respiratory rate) Helping to weigh baby Bathing baby Ward round participation	To work through at parents’ pace	Both parents
Peer support sessions—led by specialist clinical psychologists or therapists	Every two weeks	Fathers^a,b^
Ward round participation	Daily	Both parents^a^
Bite-size education classes	2-3 per week at varying times including weekend	Both parents^a,b^

^a^Any parent in the unit is welcome to participate or attend.

^b^Sessions to occur at times to suit fathers with cultural, religious, family, and work obligations, as determined through phase 1 data collection.

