## Discussion

This study will test the hypothesis that if fathers are facilitated to engage more with their baby on the NU and are better supported during the neonatal stay, both parents will experience fewer MH symptoms during their baby’s hospitalization and up to 6 weeks postdischarge. Improving parents’ MH is shown to allow greater parent-child bonding [32] and more sensitive responsiveness of mothers to their infants’ cues [33]. Mothers engaged in the FICare model have greater confidence in caregiving at the point of discharge and seek less medical support after discharge [32]. It is anticipated that these results will translate to fathers or partners.

Unlike many other studies [12,33], this study includes parents of a wide gestational age range of premature infants, including extremely premature infants and those who are invasively ventilated and at the highest risk of adverse outcomes. This is vital as research has found that fathers find the fragile appearance of their premature infants causes significant stress [34]. A focus of the study methods will be to upskill NU staff to increase awareness and understand the importance of father engagement in FICare and their MH as well as the impact on mother and child, which is in line with the NHS Long Term Plan [17].

Limitations of the study include the need for conversational English. This is required to be able to complete the standardized questionnaires, participate in the interviews and focus groups, and to be able to engage with the phase 2 provisions. The language for the phase 2 materials will be kept as simple to ensure readability and understanding. Exclusion from recruitment based on language will be monitored. The perceived research burden may disproportionately impact parents who have older children, have a greater distance to travel, limited parental leave, or who do not have English as their first language. There may also be cultural barriers to overcome when discussing MH.

A prospective cohort study was the most practical and ethical study design. The sample size and the primary outcome of the study is based on the qualitative data. A bigger sample size will be required for the study to be based on the quantitative or questionnaire data. The quantitative or questionnaire data collected in this study is to support the qualitative data and to test the feasibility of collecting such data longitudinally.

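### The phase comparison of questionnaire scores takes no account of gestation at birth, so any difference in gestation mix between the two consecutive cohorts could not be separated from the programme

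*Protocol article*

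**What the plan says.** The inclusion criteria admit "parents of 22^+0^ to 32^+6^ weeks preterm infants", recruited at "infants aged 1 to 7 days". Recruitment is sequential in two separate 9-month phases at one level 3 and one level 2 unit, with up to 20 families per phase. The protocol describes no randomisation, matching or quota by gestation.

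Under Questionnaires, the scores "at admission, discharge, and 6 weeks postdischarge will be compared between phase 1 and phase 2". The same sentence names the tests: the scores "will be compared between phase 1 and phase 2 using the Mann-Whitney test" and a paired t test. Regression is mentioned in that section only as a way to impute missing values.

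Three other statements bear on gestation:
- The Discussion presents it as a distinguishing feature that "this study includes parents of a wide gestational age range of premature infants", and adds that "fathers find the fragile appearance of their premature infants causes significant stress".
- The Abstract says that "Neonatal unit (NU) admissions for premature babies can last for months".
- Table 2 schedules the peer support sessions "Every two weeks".

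The Discussion also limits the role of the questionnaires: they support the qualitative data and test feasibility, and a larger sample would be needed to rest the study on them. The primary outcome is paternal stress assessed by interview.

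**The concern.** Gestation at birth could enter the phase comparison in three ways. It may affect the score itself, since the protocol links infant fragility to fathers' stress. It affects how old the infant is, and how long the parents have been in the unit, at the discharge and postdischarge forms. In phase 2 it may also affect how much of the programme a family receives.

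Nothing in the design balances gestation between phases, and the named tests contain only phase. A difference in gestation mix would pass directly into the estimated phase difference. The Discussion says the study will test whether both parents have fewer symptoms, and the Questionnaires section gives this comparison as its inferential analysis, so readers will take it as evidence on the programme. The limitations discussed do not include imbalance between phases.

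**Working it through.** **Plan's own figure.** The maximum sample is 20 families × 2 parents × 2 phases = 80 participants, which reproduces. The protocol gives no significance level, power, effect size or standard deviation (SD) for the scores, so no power calculation can be checked.

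**Step 1: gestation span and infant age at assessment.** From 22+0 (154 days) to 32+6 (230 days) is 76 days = 10.9 weeks. The protocol gives no length of stay by gestation. If infants go home at a common postmenstrual age P (assumed 35 to 40 weeks), age at discharge is P minus gestation at birth:
- born at 22+0: 13 to 18 weeks at discharge, 19 to 24 weeks at 6 weeks after discharge;
- born at 32+6: 2.1 to 7.1 weeks at discharge, 8.1 to 13.1 weeks at 6 weeks after discharge.

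The gap is 10.9 weeks whatever common P is assumed. On the same assumption, fortnightly peer support would offer about 6 to 9 sessions at one extreme and 1 to 3 at the other. Infant age at admission is confined to about the first two weeks.

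**Step 2: imbalance by chance.** The standard error (SE) of the difference in mean gestation is SD × √(2/20). A uniform spread gives SD = 10.86/√12 = 3.13; a more concentrated one is assumed at 2.5.
- SD 2.5: SE 0.79; 95% range ±1.5 weeks; probability of more than 1 week apart 21%.
- SD 3.1: SE 0.99 (from 3.13); 95% range about ±1.9 weeks; probability of more than 1 week apart 31%.

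**Step 3: effect on the phase difference.** With correlation r between gestation and score, a gestation difference d between phases displaces the score difference by r × d / SD. For SD 2.5 and d = 2 weeks this is 0.3 × 2/2.5 = 0.24 score SD, or 0.5 × 2/2.5 = 0.40 score SD. The SE of an unadjusted score difference is √(2/20) = 0.32 score SD.

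**Step 4: false-positive rate.** Simulation with no programme effect, 20 fathers per phase, gestation SD 2.5, two-sided 5% level, 4,000 runs per scenario. Correlations and shifts are assumptions.

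| Correlation | No shift | 1 week | 2 weeks | 3 weeks |
|---|---|---|---|---|
| 0 | 5.3% | 5.1% | 5.3% | 4.9% |
| 0.3 | 4.6% | 6.6% | 10.4% | 19.0% |
| 0.5 | 4.5% | 8.8% | 22.3% | 45.0% |

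These are rejection rates of the unadjusted Mann-Whitney test under a true population shift. A linear model with phase and gestation stayed between 4.6% and 5.5% in every scenario, including those with 15 per phase. A separate run with SD 2.8 gave 6.3% and 8.0% (1 week) and 8.6% and 18.1% (2 weeks) for correlations of 0.3 and 0.5.

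**Step 5: precision.** With no shift, adjustment multiplies the residual variance by 1 − r²: 0.91 at r = 0.3 and 0.75 at r = 0.5.

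**The case against.** The strongest reply is that chance imbalance and a true shift are different things. Chance imbalance does not inflate the error rate of the Mann-Whitney test; the no-shift column shows 4.5% to 5.3%. The higher rates need a true change in the population recruited, and the protocol gives no sign of one: the units, the eligibility criteria and the sequential recruitment are the same in both phases. By chance alone, means more than 2 weeks apart would occur in only about 1% to 4% of studies (SE 0.79 to 0.99). This stands. What remains is that a realised imbalance in this one study would displace its estimate, and the planned analysis could not separate that from the programme.

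The correlation is also assumed. The Discussion's remark on fragility gives no gradient by gestation, and says nothing about GAD-7, PHQ-9 or scores after discharge. This stands too, and is why a correlation of 0 belongs in the table.

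A reader might infer that a phase with more mature infants must look better. The documents do not support that: shorter stays would also mean less programme exposure in phase 2, so the net direction is unknown. Nor do they say that gestation fixes the length of stay; they say only that stays can be long.

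The admission comparison would reveal part of any baseline difference in stress, but would not correct the later comparisons for it.

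Finally, covariates are often left to an analysis plan, and this is a condensed article. But the article does name the tests and timepoints, and those tests carry no covariate. If a fuller plan already adjusts for gestation, the point falls away.

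**Conclusion.** The point holds as an inexpensive improvement to a stated analysis. Two small consecutive cohorts spanning almost 11 weeks of gestation are compared by tests that ignore it, with two of the three timepoints tied to discharge. Confounding arises only if the gestation mix differs and gestation is related to score. Under correlations of 0.3 to 0.5 and a true shift of 1 to 2 weeks, the false-positive rate is roughly 6% to 22%; without a true shift or a correlation it is near 5%. All of these are hypothetical, because the protocol supplies neither quantity, and they take the maximum of 20 fathers per phase, whereas saturation is expected at around 12 to 15.

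It would go too far to conclude that the planned test has an inflated error rate as it stands, or that the study's main conclusion is compromised. The questionnaires are secondary and supportive, so the weakness is confined to the quantitative contrast.

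The paired t test named in the same sentence does not help. It has no covariate either, and the phases contain different families; that pairing is a separate problem.

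**What to change.** In the Questionnaires section:
- Estimate the phase difference in each questionnaire score at each compared timepoint from a regression of the score, or its ranks, on phase and gestational age at birth in weeks. Do this separately for fathers and mothers, with a 95% CI.
- Label this estimate supportive or exploratory, in line with the Discussion.
- Keep the unadjusted Mann-Whitney result as a secondary display.
- Tabulate gestation at birth, and infant age at each assessment, by phase.
- Do not adjust for length of stay, because the programme may change it; gestation at birth is fixed beforehand.

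The cost is one degree of freedom and a change of wording. Gestation is already known from eligibility screening, so no new visit or form is needed. The text should also say that this adjustment does not remove other differences between sequential cohorts, such as calendar time or the mix of units.

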#### Sample Size

The sample size of the study is estimated based on qualitative study outcomes. A recent SR of qualitative study demonstrated that to achieve data saturation we need to interview 9 to 17 participants [24]. A focus group of 5 to 7 participants would be enough for in-depth conversations and 2 or more groups would increase the chances of successful data output [25].

In the first and second phases, up to 20 parents will be recruited (until the fathers’ interviews reach data saturation). With a father and mother each, there could be 40 participants per phase. In total, there could be 80 participants in the study.

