## Results

The study is currently ongoing. As of October 2023, 22 families, comprising 22 fathers and 17 mothers had been recruited. The SR studies have been registered with the PROSPERO database (324275 and 306760). The projected end date for data collection is around July 2024, data analysis will occur in November 2024, and publication of the study findings will occur in early 2025.

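### Mean, median or mode replacement is planned for missing questionnaire data alongside multiple imputation, with no primary method named; on whole scores it distorts the phase 1 versus phase 2 tests

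*Protocol article*

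**What the plan says.** The Questionnaires section under Methods plans between-phase comparisons of PSS:NICU, GAD-7 and PHQ-9 at admission, discharge and 6 weeks after discharge. These "will be compared between phase 1 and phase 2 using the Mann-Whitney test and the paired 2-tailed" t test. The same paragraph sets the missing-data rule: "Depending on the data type, missing data will be replaced with mean, median, or mode". The next sentence reads: "In addition, regression and multiple imputations analysis will also be used to impute or generate missing values".

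The wording about data type chooses among mean, median and mode. It does not choose between that family and the model-based methods. The article does not say whether the rule covers single items or whole scores, whether the replacement value is taken within phase or over both phases, or which approach is primary.

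On size, the Sample Size section says: "In the first and second phases, up to 20 parents will be recruited". With father and mother from each family, "In total, there could be 80 participants in the study". The Outcomes section makes stress assessed at the father's interview primary and the questionnaires secondary. The Discussion describes the questionnaire data as supporting the qualitative data and as serving "to test the feasibility of collecting such data longitudinally".

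**The concern.** Gaps are foreseeable. Parents complete three instruments at recruitment, every three weeks until discharge, and again by email at 4 to 6 weeks after discharge.

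A gap filled with an average is then counted as a real observation. If the average comes from the parent's own phase, the sample looks larger and less variable than it is, and the test rejects too often. If it comes from both phases together, the filled values are identical in the two groups and dilute any difference. One sentence therefore permits errors in opposite directions, depending on a detail that the article does not give. The second sentence offers a sounder method but does not say when it takes over, so the choice could be made after results are seen.

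At stake are the p values, intervals and effect sizes for the questionnaire-based secondary outcomes.

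**Working it through.** **Inputs from the article.** At most 20 fathers and 20 mothers per phase. The participant ceiling reproduces: 20 families × 2 parents × 2 phases = 80. It rests on qualitative saturation, so there is no power calculation to reproduce.

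**Assumptions.** Missing fraction m of 10, 20, 30 or 40%, equal in both phases and completely at random; two-sided 5% level; normally distributed scores. The article states none of these. I used an unpaired t test because the two phases enrol different families, and Mann-Whitney because the article names it.

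**Within-phase mean filling: standard error.** Let n = 20 and o = n(1 − m) be the number observed per phase. Filled values add nothing to the sum of squares, but they raise the divisor from o − 1 to n − 1 and the apparent sample size from o to n. Hence

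reported SE ÷ valid SE = √[ o(o − 1) / (n(n − 1)) ], with n(n − 1) = 380.

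- 10% missing, o = 18: √(306/380) = 0.897
- 20% missing, o = 16: √(240/380) = 0.795
- 30% missing, o = 14: √(182/380) = 0.692
- 40% missing, o = 12: √(132/380) = 0.589

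**Within-phase mean filling: type I error.** The filled-data t statistic is the valid one divided by this ratio. The test therefore rejects when a t variable on 2(o − 1) degrees of freedom exceeds 2.024 × ratio in absolute value, where 2.024 is the 5% critical value on 38 degrees of freedom. The cut-offs are 1.817, 1.609, 1.401 and 1.193 on 34, 30, 26 and 22 degrees of freedom. Simulation used 6,000 runs per cell.

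| Missing | t test, exact | t test, simulated | Mann-Whitney, simulated |
|---|---|---|---|
| 10% | 7.8% | 8.2% | 9.3% |
| 20% | 11.8% | 11.8% | 15.6% |
| 30% | 17.3% | 17.5% | 25.8% |
| 40% | 24.5% | 24.9% | 42.2% |

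Filling with the within-phase median is similar: 8.1, 11.5, 17.9 and 26.8% for the t test. Leaving the missing values out keeps the error at 4.6 to 5.0% (t test) and 4.2 to 4.8% (Mann-Whitney).

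**Overall-mean filling.** Each phase mean becomes (1 − m) × observed mean + m × common value. The common value cancels, so the expected difference is (1 − m) times the true one. For a true 0.50 SD:

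- 10%: 0.90 × 0.50 = 0.45 SD
- 20%: 0.80 × 0.50 = 0.40 SD
- 30%: 0.70 × 0.50 = 0.35 SD
- 40%: 0.60 × 0.50 = 0.30 SD

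In simulation the type I error stays near 5% on this branch. Inflation and attenuation are therefore alternatives and do not occur together.

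**The case against.** The strongest reply has three parts.

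1. **The questionnaires are secondary.** The Discussion says that a larger sample would be needed to base the study on them. This stands and lowers the severity. It does not remove the point, because the article still commits to inferential tests on these scores.

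2. **The wording can be read charitably.** Simple replacement might be meant for single items, with multiple imputation for whole scores or as a sensitivity analysis. PSS:NICU has 46 items, so odd item gaps are likely, and filling a few from the same person's other items does little harm. The text permits this reading but does not state it. A reader might infer that the two sentences flatly contradict each other. That goes too far: the second is worded as an addition, so the rules are unordered and unscoped, not strictly incompatible.

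3. **An analysis plan may settle the detail.** That would answer a mere omission. Here the article states a poor method as something that will be done.

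Some stronger readings should be set aside. The Results section reports that "22 families, comprising 22 fathers and 17 mothers had been recruited", and a reader might infer that scores would be invented for the five mothers not enrolled. Maternal participation is optional, and someone who never joined has no missing data. Nor does the text propose filling scores after an infant's death. Filling gaps for a test does not stop completeness from being reported. The article also gives no evidence that distressed parents respond less often, and the calculation above does not assume it.

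**Conclusion.** The point holds at moderate severity. A stated rule, if applied to whole scores, either makes the tests anticonservative or shrinks the phase difference, and the article names no primary method. On the within-phase branch, the reported standard error is 0.90 down to 0.59 of the valid one as missingness goes from 10 to 40%. With a few per cent missing the effect would be small; with a fifth or more missing it would materially change how a p value should be read.

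These sizes rest on the assumed missing fractions, 20 per phase, normal scores and data missing at random. They are a range, not a prediction. The highest figures are one end of one branch and should not be quoted as the study's expected error rate. A reader might also infer that the main conclusion is at risk. It is not: the primary outcome comes from interviews, and this rule does not touch it.

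**What to change.** In the Questionnaires section:

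- Remove mean, median or mode replacement of whole questionnaire scores.
- Keep simple within-person proration only where a few items of a scale are missing, with the limit stated in advance.
- Name one primary method for missing whole questionnaires: either a likelihood-based repeated-measures model on all observed scores, or multiple imputation that includes phase and earlier scores. At about 20 per phase, either model must be kept small.
- Label any other method as a sensitivity analysis.
- Report questionnaire completeness by phase and time point as part of the feasibility aim in the Discussion.

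This is a change of wording plus slightly more analysis. Nothing changes for participants or data collection. Intervals will be wider than after single-value filling within phase, because they will reflect the data actually observed.
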